## Abstract

**Background:**

The 2016 World Health Organization Antenatal Guidelines and the 2015 South African Maternal and Child Health Guidelines recommend one early antenatal ultrasound scan to establish gestational age and to detect multiple pregnancies and fetal abnormalities. Prior research indicates that ultrasound scan can also increase parental–fetal attachment. We aim to establish whether, compared to routine care, messages to promote parental attachment and healthy child development, conducted during one or two pregnancy ultrasound scans, improve early child development and growth, exclusive breastfeeding, parental–child interactions and prenatal and postnatal clinic attendance.

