**Discussion:**

Evidence from high-income countries suggests that first-time prospective mothers and fathers enjoy seeing their fetus during ultrasound scan and that it is an emotional experience. A number of studies have found that ultrasound scan increases maternal attachment during pregnancy, a predictor of positive parent–infant interactions which, in turn, promotes healthy infant development. It is generally agreed that studies are needed which follow up parental–child behaviour and healthy child development postnatally, include fathers and examine the construct in a wider diversity of settings, especially in low and middle-income countries. Testing the added benefits of pregnancy ultrasound scan for child development is a gap that the proposed trial in South Africa seeks to address.

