## Methods

### Objectives

The trial will evaluate the potential benefits of US on early childhood development and child care by augmenting a routine antenatal service currently provided mainly in tertiary public health facilities in South Africa, with plans to be rolled out to district hospitals. The goal of the intervention is to increase parental investment not only in child survival, but also for the well-being and healthy growth and development of their child. We aim to establish whether, compared to routine care, messages about fetal and child development delivered during one (< 25 weeks) or two (< 25 weeks and again < 36 weeks) fetal USs improve ECD and growth, exclusive breastfeeding, mother/father–infant attachment, maternal and paternal well-being, father involvement and prenatal and postnatal clinic attendance.

Specific objectives are to evaluate whether child development messages delivered during one or two USs:
Improve early child developmentImprove infant breastfeeding practices and healthy child growthImprove parent–infant attachment and interaction during pregnancy and 6 months after birthIncrease paternal engagement in a young child’s development and care

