### Design

Eligible mothers will be randomised to one of three arms: Arm 1, the control group, will receive standard practice of care during pregnancy; Arm 2 will receive the child development intervention at the first research ultrasound visit; and Arm 3 will receive the intervention at two research ultrasound visits. All mothers, infants and partners (where available) will be followed-up 6 weeks and 6 months postnatally for assessments. Participants will continue to receive routine antenatal, perinatal and postnatal care as provided by the tertiary care facility from which all participants are being recruited.

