### Intervention

Women will be randomised to one of three arms on recruitment at CHBH < 25 weeks gestation after having a fetal ultrasound examination as part of routine antenatal hospital services. The women will be blind to their arm allocation and remain blinded until study completion. Using computer-generated simple randomisation, each consecutive woman screened will be randomly allocated to a study arm. Research assistants responsible for screening will receive the study arm numbers for allocation from the study coordinator on a daily basis. The allocation sequence will be concealed from the research assistants enrolling the participants. Women recruited for Arm 1 will act as the control group and will receive one further standard US at DPHRU < 25 weeks gestation, when they will receive standard fetal growth measurements but no child development messages.

In addition to their routine antenatal US at CHBH, women recruited to Arm 2 will receive an additional US < 25 weeks gestation at DPHRU, during which they will receive messages to promote early childhood development. During the US session, the sonographer will talk with the mother and partner, if present, about the fetus’ sensory development and capacity for learning, fetal responsivity to the environment, maternal well-being and the dependence of the fetus on maternal and paternal health and well-being before and after birth.

In addition to their routine antenatal US at CHBH, women recruited to Arm 3 will receive two additional USs at DPHRU, one < 25 weeks gestation (early US) and another < 36 weeks gestation (late US). They will receive the same child development messages as mothers in Arm 2 at the first US. During the second US, in addition to childhood development messages, the sonographer will encourage the woman and her partner, if present, to personalise the baby, strengthen intentions to exclusively breastfeed, talk and sing to the child before and after birth, and counsel them on how to respond to their young infant’s emotional and learning needs.

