Partner involvement and interest in the baby is encouraged by inviting partners to attend the ultrasound sessions of women in all three arms. For mothers recruited to Arms 2 and 3, digital ultrasound images and a photograph of the woman (with her partner where present) having the US will be sent to parents via WhatsApp and printed images given to the parents. A small baby book with the child development messages, as appropriate to the arm, is given to the mothers in Arms 2 and 3, and they are encouraged to paste the printed pictures into the book and to share the US images and photographs with family and friends.

Two qualified and registered sonographers will be trained to deliver the intervention and a Philips HD9 Ultrasound System will be used to conduct all USs. Due to the nature of the intervention, the sonographers will not be blind to the mother’s arm allocation.

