## Discussion

While ultrasound examination has long been regarded as having potential to be transformative and to improve parental behaviour [14], as well as commitment to the growing child [12], this hypothesis has only been tested in a few studies in high-income countries, fewer of which were randomised control trials [55].

There is clear evidence from high-income countries that the first time a prospective mother sees an image of their fetus during US is an emotionally enjoyable experience, which parents report intensifies their attachment to the coming baby. This is true also of prospective fathers [22, 56], and is reported as being an important bonding experience for the family [57]. A number of studies have examined the impact of ultrasound examination on maternal attachment [24, 58, 59]. However, women’s experiences of US are dependent on the context and the behaviour of the sonographer, with some women reporting feeling objectified and poorly informed during the experience [60].

Research on the emotional and relationship effects of early US are important because maternal (and presumably paternal) representations of the coming baby are significant predictors of parent–infant interactions which, in turn, affect healthy infant development [61, 62]. A recent review of interventions indicated that awareness programmes, most commonly involving pregnancy US, were amongst the most promising interventions to increase parent–fetal attachment [55]. There is agreement that studies are needed which follow up parental–child behaviour and healthy child development postnatally, include fathers and examine the construct in a wider diversity of settings, including in low and middle-income countries. Testing the added benefits of pregnancy US for child development is the gap that this proposed randomised control trial in South Africa seeks to address.

Should this trial demonstrate feasibility and improvement in the specified intermediate and outcome measures, the next step would be a pragmatic trial situated in the health-care system, with longer-term outcomes and cost-effectiveness estimations.

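### The aim names routine care as the comparator, but the control arm also gets a research scan, so no contrast tests the intervention against routine care alone or isolates an ultrasound effect

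*Protocol article*

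**What the plan says.** Three places in the protocol article name the comparator as usual care. The abstract's Background gives the aim as "We aim to establish whether, compared to routine care, messages to promote parental attachment and healthy child development" improve outcomes. The Objectives section repeats it: "We aim to establish whether, compared to routine care, messages about fetal and child development delivered during one" or two scans. The Design section says "Arm 1, the control group, will receive standard practice of care during pregnancy" and mentions no extra scan.

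Two places describe a different control. The abstract's Methods gives Arm 1 the hospital scan and then a second standard scan at the research site. The Intervention section says that women in Arm 1 "will receive one further standard US at DPHRU < 25 weeks gestation", with growth measurements but without messages. Table 1 lists this early scan without messages under Interventions.

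Arms 2 and 3 also receive items that Arm 1 does not. Under Intervention, "digital ultrasound images and a photograph of the woman (with her partner where present) having the US will be sent to parents via WhatsApp", printed images are handed over, and a baby book carrying the messages is given.

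Some statements speak of ultrasound itself. Objectives: "The trial will evaluate the potential benefits of US on early childhood development and child care". Abstract, Discussion: "Testing the added benefits of pregnancy ultrasound scan for child development is a gap" that the trial addresses. The main Discussion repeats this almost word for word: "Testing the added benefits of pregnancy US for child development is the gap".

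**The concern.** The aim and the Design section promise one comparison, and the arms as delivered provide another. If the results are reported in the words of the aim, the conclusion will name a comparator that nobody in the trial received.

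This matters because the protocol's own rationale is that seeing the fetus may in itself strengthen attachment. On that rationale the control scan cannot be assumed inert. A null or small Arm 2 versus Arm 1 difference would then not mean that the package adds little to routine care. An Arm 3 versus Arm 1 difference could not be credited to the messages alone. The main Discussion proposes a pragmatic trial within the health service as the next step, and whoever plans that trial needs to know what the reference condition was.

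**Working it through.** **The plan's own figure.** Inputs from Recruitment and Data analysis: difference 0.5 SD, two-sided alpha 0.05, power 90%, attrition 15%.

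- n per arm = 2 × (1.960 + 1.282)² / 0.5² = 84.1, rounded up to 85. Solving with the t distribution gives 85.03.
- 85 / (1 − 0.15) = 100 per arm, and 3 × 100 = 300.

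The stated 85, 100 and 300 are reproduced. This point disputes no number.

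**What each arm receives beyond hospital care** (abstract Methods; Intervention):

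| | Research scans | Message sessions | Images, photograph, book |
|---|---|---|---|
| Routine care alone | 0 | 0 | no |
| Arm 1 | 1 | 0 | no |
| Arm 2 | 1 | 1 | yes |
| Arm 3 | 2 | 2 | yes |

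The first row is the comparator named in the aim. No trial arm occupies it. Only research scans are counted, because the article does not cap the number of scans in tertiary routine care.

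**What the contrasts estimate.** Write r for the mean outcome under routine care alone, s1 for the effect of the first research scan, p1 for the message package given with it, s2 for the second research scan and p2 for the second session. Additivity is assumed only to keep the notation simple.

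- Arm 1 = r + s1
- Arm 2 = r + s1 + p1
- Arm 3 = r + s1 + p1 + s2 + p2

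Subtracting:

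- Arm 2 − Arm 1 = p1
- Arm 3 − Arm 1 = p1 + p2 + s2
- Arm 3 − Arm 2 = p2 + s2

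The comparison with routine care would be:

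- Arm 2 − r = p1 + s1
- Arm 3 − r = p1 + p2 + s1 + s2

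In the arm means, r and s1 appear only as the sum r + s1, so s1 cannot be recovered and neither comparison with routine care can be estimated. Likewise s2 appears only with p2, because no arm has a second research scan without messages. An ultrasound effect is therefore not separable in any contrast.

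**Size.** Each contrast against Arm 1 differs from its routine-care counterpart by exactly s1. The documents give no value or sign for s1 or s2. The section on benefits of pregnancy ultrasound reports mixed evidence: a 1999 review found none that seeing the baby stimulates attachment, while later studies report positive effects. Zero is therefore within the plausible range.

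**The case against.** The strongest reply is that the question is about messages, and the design answers it. The abstract's Methods, the end of the Background and the specific objectives all concern messages delivered at a scan. Giving Arm 1 a scan without messages holds the scan count equal against Arm 2, which is a strength. The extra scan is disclosed in the abstract itself. All of this stands. A reader might infer that the trial cannot answer its main question, and the documents do not support that.

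A second reply is that the Background openly declares messages together with one or two additional scans as the intervention, so the Arm 3 bundle is intended. That stands too: testing a package is ordinary practice, and the book is a medium for the messages. It does not rescue the comparator label, since the control also receives one additional scan.

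Third, the phrase about added benefits can be read as using the scan as a platform for promoting child development. That is a fair reading, but the wording also admits a scan-only reading, which no contrast supports.

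Three further inferences are tempting and should not be drawn:

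- *A fixed share of the Arm 3 effect is due to the scan.* With an assumed package effect of 0.3 SD and scan effect of 0.1 to 0.2 SD, the share is 0.1/0.4 = 25% to 0.2/0.5 = 40%. That gives the second session no effect, although it adds new content. Give it 0.3 SD and the share is 0.1/0.7 = 14% to 0.2/0.8 = 25%. With no scan effect it is zero. The inputs are invented, so no figure is defensible.
- *The trial is underpowered.* If 0.5 SD were the effect against routine care and the control scan delivered 25% or 50% of it, the Arm 2 versus Arm 1 difference would be 0.375 or 0.25 SD, with power of about 69% or 37% at 85 per arm. But the sample-size statement sets 0.5 SD as a difference between arms, so it already refers to Arm 1 as delivered.
- *Retention contact biases the clinic-attendance comparison.* That contact is described for all participants and does not by itself favour any arm.

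**Conclusion.** The point holds as a mismatch between the stated comparator and the delivered control. The abstract's aim, the Objectives and the Design section say routine care or standard practice. The abstract's Methods and the Intervention section add a standard research scan. As a result, no contrast estimates the intervention against routine care alone, and none isolates an effect of ultrasound. This follows from the composition of the arms and needs no assumption about effect sizes.

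The consequence lies in what may be concluded. No sample size or test changes. The distance from a routine-care comparison is the unknown effect of one scan, which could be nil, so neither an amount nor a direction of error can be claimed. The scan-matched control is a sound choice for the messages question and should stay.

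**What to change.** 1. In the abstract, Objectives and Design, define the comparator as routine care plus one additional standard research ultrasound without messages, so that these places agree with the abstract's Methods and the Intervention section.
2. State that Arm 2 versus Arm 1 estimates the message package (messages, book, images, photograph) at equal scan counts.
3. State that Arm 3 versus Arm 1 estimates the two-session package together with one more scan, and that the two contributions cannot be separated.
4. Limit conclusions to these contrasts. Reword the statements on benefits of ultrasound in the abstract's Discussion, the Objectives and the main Discussion so that they do not imply a scan-only effect.
5. While doing so, relabel the pairwise comparisons under Data analysis, which list Arm 1 against control although Arm 1 is the control.

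The cost is wording. No new arm, data or analysis is needed, and closed recruitment is no obstacle. A claim about ultrasound itself, or about routine care alone, would need arms that this trial does not have.

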**Methods:**

The effect of messages to sensitise mothers and fathers to fetal development will be tested in a three-armed randomised trial with 100 mothers and their partners from Soweto, Johannesburg in each arm. The primary outcome is child development at 6 months postnatally. Secondary outcomes include infant feeding, parental attachment and interaction, parental mental health and infant growth, assessed at 6 weeks and 6 months. Parents in Arm 1 receive a fetal ultrasound scan < 25 weeks during routine antenatal care at tertiary hospitals, and a second standard ultrasound scan at the research site within 2 weeks. Arm 2 participants receive the routine antenatal ultrasound scan and an additional ultrasound scan < 25 weeks at the research site, together with messages to promote parental attachment and healthy child development. Arm 3 participants receive the routine ultrasound scan and two additional ultrasound scans at the research site, < 25 weeks and < 36 weeks, together with messages to promote parental attachment and healthy child development.

**Discussion:**

Evidence from high-income countries suggests that first-time prospective mothers and fathers enjoy seeing their fetus during ultrasound scan and that it is an emotional experience. A number of studies have found that ultrasound scan increases maternal attachment during pregnancy, a predictor of positive parent–infant interactions which, in turn, promotes healthy infant development. It is generally agreed that studies are needed which follow up parental–child behaviour and healthy child development postnatally, include fathers and examine the construct in a wider diversity of settings, especially in low and middle-income countries. Testing the added benefits of pregnancy ultrasound scan for child development is a gap that the proposed trial in South Africa seeks to address.

**Trial registration:**

Pan African Clinical Trials Registry, PACTR201808107241133. Registered on 15 August 2018.

## Background

More than 250 million children younger than 5 years of age in low and middle-income countries (43% of the total globally) are at risk of not reaching their developmental potential because they are stunted or live in extreme poverty. This rises to 70% of young children in sub-Saharan Africa, which has the highest risk burden in the world [1]. In South Africa (SA), the risk is 39% of children under 5 years of age, with knock-on losses of human capital due to inadequate school learning and low earning capacity [2]. The Global Strategy for Women’s, Children’s and Adolescents’ Health [3] and the fourth Sustainable Development Goal [4] recognise the importance of promoting early childhood development (ECD) to ensure that children survive *and* thrive, and rightfully fulfil their human potential and contribute productively to their families and societies.

The 2017 *Lancet* Series *Advancing Early Childhood Development: From Science to Scale* recommended that the contacts which the Reproductive, Maternal, Newborn and Child Health (RMNCH) services have with pregnant women, parents and families are important entry points to promote ECD [5]. Further, the series noted that many effective programmes for ECD are currently built on health services, demonstrating the feasibility of this approach for taking interventions to promote ECD to scale [2, 6].

In 2015, South Africa adopted a National Integrated Early Childhood Development Policy that mandates the health sector to lead in providing services for children and families in the first 1000 days of life, starting from conception, in collaboration with other relevant sectors. Taking this up, the National Department of Health (NDoH) launched a Side-by-Side campaign [7] to bolster support for pregnant women and families with young children, and revised the Road to Health Booklet to emphasise survive and thrive.

The 2015 NDoH Guidelines for Maternity Care in SA [8] recommend that all pregnant women attending a district hospital should have access to one ultrasound scan (US) at 18–20 weeks gestation. The purpose of the US is to confirm an intra-uterine pregnancy, fetal viability, the number of fetuses, gestational age, location of the placenta and amniotic fluid volume. The 2016 WHO Antenatal Guidelines recommend one US before 24 weeks gestation “to estimate gestational age, improve detection of fetal abnormalities and multiple pregnancies, reduce induction for post-term pregnancy, and improve a women’s pregnancy experience” [9], Recommendation B.2.4).

Taking advantage of the SA and WHO recommendations that pregnant women have an ultrasound examination before 24 weeks gestation, the aim of this three-arm trial is to assess whether messages to promote ECD delivered during pregnancy and one or two additional ultrasound examinations will increase parental investment in ECD, as indexed by infant development, nutrition and growth, and the quality of parent–child relationships 6 weeks and 6 months post partum.

### Benefits of pregnancy ultrasound scan

In addition to the survival and health benefits of US reviewed by the WHO in preparation of the guidelines [10], the possibility is raised that US may increase antenatal clinic (ANC) use [11], particularly in view of the recommendation that ANC visits be increased from four to eight. However, the evidence on ultrasound examination, including any psychological benefits, is derived almost solely from high-income countries (HICs).

Early pregnancy US has been routine in HICs for more than 30 years. At the time of introduction of US, studies reported positive parental reactions to seeing images of the fetus [12, 13], that parents enjoyed the experience and that they found it useful to receive information during US [14]. Reading et al. [15] commented on the potential of US to change parental behaviour for the better, such as smoking cessation during pregnancy. Rothenberg speculated that further research could “lead to the development of ultrasound use patterns designed to enhance maternal attachment”, and that “the psychosocial dimension of ultrasound scanning seems obvious to patients and personnel in the field” [16], p. 171).

In qualitative studies, both mothers and fathers report enjoying the US experience and that the presence of the father seemed to have a beneficial effect on the mother [17]. A 1999 review concluded that there was as yet no evidence of increases in health behaviours following US, nor that “seeing the baby” stimulates parental–fetal attachment [18]. Based on their review, Baillie et al. cautioned that “Practitioners and decision makers should be wary of over-interpreting enjoyment of a procedure as evidence of its therapeutic power” ([18], p. 149). Later studies, however, report positive effects of US on maternal and paternal attachment [19–22] but only a few have examined the effects of US on attachment after birth [23, 24].

US studies conducted in sub-Saharan Africa have principally focused on US costs, maintenance, training, human resources, acceptability and other aspects of feasibility, including in Ghana [25], Kenya [26], Zambia [27], Nigeria [28–30], Rwanda [31], South Africa [32], Tanzania [33, 34] and Uganda [35, 36]. In general, US is thought to enhance antenatal care through confirmation of pregnancy status and more accurate estimation of gestational age, but concerns remain about feasibility of wide-scale use in low and middle-income countries and the potential misuse of US for sex determination in countries with a high preference for male children [37]. A recent, large, cluster-randomised control trial in Pakistan, Kenya, Zambia, DRC and Guatemala suggested that US did not increase ANC use or hospital births [38]. However, a review in sub-Saharan Africa concluded that “The potential benefits of obstetric ultrasound are yet to be fully realized in SSA due to challenges ranging from individual patients to institutional and national policies. While there may be conflicting evidence on the impact of universal access on perinatal outcomes, the region presents many research opportunities that could provide answers to these questions” [39], p. E58).

Point-of-care ultrasound (PoCUS) makes scale-up more feasible [39, 40] and evidence for its use more positive than standard US. A recent review [41] concluded that in every study in which it was examined in low and middle-income countries, PoCUS increased antenatal clinic attendance and assisted with the identification and treatment of conditions associated with maternal and neonatal morbidity in under-resourced settings. PoCUS thus has the potential to bring much-needed services to women in rural communities and in poor countries, many of whom need these services most. In addition to increasing access to services, US has also been found to provide an opportunity to engage fathers [42], with the potential of garnering support for the expectant mother and their child and potential sharing of child-care responsibilities.

This study examines US augmented with messages about fetal and infant development and the importance of parent well-being and infant care on postnatal care and early childhood development. We hypothesise that one or two USs with messages about fetal and infant development will have a positive effect on infant development 6 months postnatally, as well as on parental well-being, parent–child attachment, infant feeding and growth and use of preventive health-care services.

